# Remote Assessment of Lung Disease and Impact on Physical and Mental Health (RALPMH): Protocol for a Prospective Observational Study

**DOI:** 10.2196/28873

**Published:** 2021-10-07

**Keywords:** mHealth, COVID-19, mobile health, remote monitoring, wearables, internet of things, lung diseases, respiratory health, mental health, cardiopulmonary diseases

## Abstract

**Background:**

Chronic lung disorders like chronic obstructive pulmonary disease (COPD) and idiopathic pulmonary fibrosis (IPF) are characterized by exacerbations. They are unpleasant for patients and sometimes severe enough to cause hospital admission and death. Moreover, due to the COVID-19 pandemic, vulnerable populations with these disorders are at high risk, and their routine care cannot be done properly. Remote monitoring offers a low cost and safe solution for gaining visibility into the health of people in their daily lives, making it useful for vulnerable populations.

**Objective:**

The primary objective is to assess the feasibility and acceptability of remote monitoring using wearables and mobile phones in patients with pulmonary diseases. The secondary objective is to provide power calculations for future studies centered around understanding the number of exacerbations according to sample size and duration.

**Methods:**

Twenty participants will be recruited in each of three cohorts (COPD, IPF, and posthospitalization COVID). Data collection will be done remotely using the RADAR-Base (Remote Assessment of Disease And Relapse) mobile health (mHealth) platform for different devices, including Garmin wearable devices and smart spirometers, mobile app questionnaires, surveys, and finger pulse oximeters. Passive data include wearable-derived continuous heart rate, oxygen saturation, respiration rate, activity, and sleep. Active data include disease-specific patient-reported outcome measures, mental health questionnaires, and symptom tracking to track disease trajectory. Analyses will assess the feasibility of lung disorder remote monitoring (including data quality, data completeness, system usability, and system acceptability). We will attempt to explore disease trajectory, patient stratification, and identification of acute clinical events such as exacerbations. A key aspect is understanding the potential of real-time data collection. We will simulate an intervention to acquire responses at the time of the event to assess model performance for exacerbation identification.

**Results:**

The Remote Assessment of Lung Disease and Impact on Physical and Mental Health (RALPMH) study provides a unique opportunity to assess the use of remote monitoring in the evaluation of lung disorders. The study started in the middle of June 2021. The data collection apparatus, questionnaires, and wearable integrations were setup and tested by the clinical teams prior to the start of recruitment. While recruitment is ongoing, real-time exacerbation identification models are currently being constructed. The models will be pretrained daily on data of previous days, but the inference will be run in real time.

**Conclusions:**

The RALPMH study will provide a reference infrastructure for remote monitoring of lung diseases. It specifically involves information regarding the feasibility and acceptability of remote monitoring and the potential of real-time data collection and analysis in the context of chronic lung disorders. It will help plan and inform decisions in future studies in the area of respiratory health.

**Trial Registration:**

ISRCTN Registry ISRCTN16275601; https://www.isrctn.com/ISRCTN16275601

**International Registered Report Identifier (IRRID):**

PRR1-10.2196/28873

## Introduction

### Background

Patients with chronic conditions like chronic obstructive pulmonary disease (COPD) and interstitial lung disease (ILD) must often manage their diseases from a community setting, and this presents natural challenges in monitoring patient health status. Currently, COVID-19 presents additional challenges, especially for vulnerable patients with pre-existing conditions and diseases where, due to shielding, their routine care cannot be performed properly [1]. Remote monitoring of the physiology and symptoms of patients via wearable devices could provide convenient and useful advantages over conventional care for patients managing their health care in real-world settings. These can include detailed information on their historical health, current health status, and potential to intervene during acute events, as well as prognosis of future health and disease trajectory. Remote monitoring may also provide an opportunity during events like the COVID-19 pandemic to safely monitor disease exacerbation or progression without putting patients in situations where risk of exposure to COVID-19 is increased.

### Remote Monitoring

This study aims to use the open-source RADAR-Base (Remote Assessment of Disease and Relapse) mobile health (mHealth) platform to collect and analyze multiple data sets associated with respiratory disorders. Several cardiopulmonary parameters are now available in modern consumer wearable devices, and due to close coupling of the heart and lungs, measurements of the functions of these organs are expected to provide good characterization of diseases. This study will include continuous data collected from wearable devices (eg, heart rate [HR], respiratory rate, and oxygen saturation [SpO_2_]), including pulse oximeters and spirometers, mobile phones (audio), digital tests, and smartphone symptom questionnaires.

The RADAR-Base community emerged from the Innovative Medicines Initiative (IMI) project RADAR-CNS (Remote Assessment of Disease and Relapse – Central Nervous System), where a consortium of clinicians, developers, researchers, patient organizations, and European Federation of Pharmaceutical Industries and Associations (EFPIA) partners joined forces to explore the potential use of sensor data from wearable devices like fitness trackers and smartphones in research and health care. The RADAR-Base platform is a scalable and interoperable mHealth platform that provides capabilities for remote monitoring passively (eg, sensor data, wearables, and internet of things [IoT]) and actively (eg, questionnaires and digital tests). The platform developed at King’s College London and the Hyve in the Netherlands is already being used in a number of large-scale longitudinal mental and physical health–related disorder projects [2,3]. The complete RADAR-Base technology stack is available under an Apache 2 open-source license and is supported by an active community of developers, researchers, and clinicians who focus on continuously improving data quality, user experience, and validation, and extending the platform with new features and data sources.

All the data collected and aggregated using the RADAR-Base platform are standardized using Avro schemas [4] and harmonized across various data streams.

RADAR-Base also provides the potential to respond or alert in near real time based on some state of the data being collected; this could include identifying, for example, an exacerbation and triggering a response, such as an intervention or follow-up questionnaire/test or confirmation.

This pilot will help answer how remote monitoring may be used for lung disease patients, who in many cases may be shielding during the COVID-19 pandemic because of being at high risk and being vulnerable, and offers additional benefits, including participation without additional risk of travel or interaction with hospital staff.

### ILD

ILD, or lung fibrosis, is one of a spectrum of fibrotic diseases associated with aging, obesity, diabetes, and pollution, which are responsible for approximately 45% (9/20) of premature deaths in Western Europe. Of over 90,000 patients in the United Kingdom with ILD, approximately 30,000 have idiopathic pulmonary fibrosis (IPF), which is the most severe form. IPF is a disease of unknown etiology that is more frequent in males and presents mainly in the sixth and seventh decades of life [5]. There is no cure, and the median survival of 3 to 5 years following diagnosis is worse than that for many cancers. As the fibrosis progresses, there is impaired pulmonary function, respiratory failure, and ultimately death. Throughout its course, IPF has significant effects on physical (dyspnea, dry cough, weight loss, and fatigue) and social (recreational activities and relationships) functions, with severe consequences for the patient’s health-related quality of life (QoL). Clinical courses are punctuated by episodes of worsening disease that may result in death. These acute exacerbations of IPF (AE-IPF) are estimated to occur in 4% to 20% (1-4 in 20) of patients each year, but the true incidence and impact are not known [6].

Management of AE-IPF involves establishing the diagnosis and excluding other causes of increasing dyspnea, excluding infection, and considering the use of steroids, antibiotics, and/or anticoagulation, none of which has been shown to be of benefit. The trajectory of patients with IPF is heterogeneous with great variability in the disease course. Some progress slowly, whereas others progress more rapidly, and this can cause emotional distress and anxiety. Patient-reported outcome measures are used to measure health-related QoL, assess symptoms, and evaluate disease progression. The management of patients with IPF is multifaceted and consists of patient education and support, regular outpatient surveillance, symptom relief, pulmonary rehabilitation, annual vaccinations to prevent respiratory infection, identification and management of AE-IPF, supplemental oxygen, management of comorbidities, and ultimately palliative care or, in a minority of patients, referral for lung transplantation [7].

Two antifibrotic treatments (pirfenidone and nintedanib) are available for patients who meet the stringent National Institute for Health and Care Excellence (NICE) criteria. They neither cure nor reverse the fibrosis and have little impact on symptoms, but they have been shown to reduce the rate of lung function decline, and pirfenidone has been shown to reduce AE-IPF and improve progression-free survival [8].

With regard to the impact on health care systems, IPF is a cost- and resource-intensive disease encompassing hospitalization, home care, long-term care, and antifibrotic therapy. The full health burden on the National Health Service (NHS) and UK economy is unknown, but data from the British Lung Foundation and projected estimates from our patient cohort suggest that there are approximately 30,000 IPF diagnoses each year. Health care costs alone for IPF are estimated at US $15,000 to $78,000 per patient-year [6].

Regarding the need for biomarkers for precision management, the disease progression in IPF is highly variable with individuals experiencing very different trajectories. Response to antifibrotic therapy is also inconsistent with some patients tolerating the medication well and others experiencing significant side effects. Currently, there is a lack of valid endpoints, apart from a change in forced vital capacity, which has poor sensitivity and specificity to accurately assess disease activity or response to treatment [9]. This makes it difficult to predict individual prognosis or reliably detect early treatment response or failure, which is important for developing treatment plans and providing patients with accurate prognostic information, which allows them to plan for their future. Remote monitoring may allow clinicians and patients access to more granular longitudinal data on disease progression, the rate of AE-IPF, and effects on QoL, and begin to offer personalized treatment approaches in this cohort. Remote monitoring may also reduce patients’ attendance at the hospital for clinical follow-up or when taking part in clinical trials of novel agents. Remote monitoring may allow the early identification of AE and a better understanding of the frequency and impact of these events, and may provide the potential to develop clinical trials of treatments in these patient groups.

### COPD

COPD is a common long-term condition of the lungs that is usually caused by cigarette smoking. In addition to daily symptoms and limitations in activities, patients are prone to developing chest infections called “exacerbations” [10,11]. Exacerbations are a significant problem. They are unpleasant for patients and sometimes severe enough to cause hospital admission (and therefore NHS pressures) and death. Reducing the impact of exacerbations is very important [12]. We have previously shown that earlier treatment of COPD exacerbations results in faster recovery and reduced chance of hospital admission. Helping patients to detect exacerbations early is therefore important. We have also recently shown that monitoring HR and oxygen saturation via a finger probe may assist in this, especially overnight when the physiological signal is cleaner [13]. Integration of these signals with additional symptom data and use of innovative data analysis methodology are likely to result in the greatest chance of supporting the early detection of exacerbations and assessment of disease progression. This is even more important in the era of COVID where many patients with COPD are classified as “clinically extremely vulnerable,” and thus, remote monitoring provides the safest way to support management in partnership with their clinicians.

### Posthospitalization COVID-19 Lung Disorders

Recovery from COVID-19 has many unknowns, especially in the long term [14]. The symptoms of COVID-19 have varied among those who have tested positive. Some have displayed no symptoms, while others have developed severe pneumonia, progressing to lung injury, and acute respiratory distress syndrome, as well as pulmonary fibrosis in the longer term. Notably, the consequences of COVID-19 include effects on other organs, including the heart, kidneys, and brain. Correspondingly, a diverse set of associations have been observed that together have been called “long COVID,” which involves prolonged and delayed recovery from the acute illness, including fatigue, shortness of breath, and cough, associated with mental health and neurological disorders, such as fatigue, trauma, and anxiety/depression [15,16]. For those who were hospitalized and have since been discharged, it is not yet clear what their medical, psychological, and rehabilitation needs will be to enable them to make as full a recovery as possible.

Given this need to follow-up with COVID-19 patients after hospitalization, we consider remote monitoring to provide some key opportunities. First, observation of chronic symptoms will necessitate home-based monitoring, as the scope of regularly interfacing with participants in the clinic may be limited due to the likelihood of further periods of lockdown and self-isolation of this population. Second, there needs to be a greater focus on understanding how daily life is affected by this disease. Remote monitoring, therefore, provides an ideal opportunity to collect multiple continuous data streams from participants to report on physiology, QoL, and environmental and functional aspects. Building on our existing experience in using wearables to monitor participants who develop COVID-19 [17], we aim to extend this to enable detailed observation of patients as they experience symptoms of long COVID. By using a longitudinal, high frequency, and largely passive monitoring approach, we aim to develop an understanding of the disease trajectory and the fluctuation of symptoms.

### Theoretical Framework

The Remote Assessment of Lung Disease and Impact on Physical and Mental Health (RALPMH) study will use a prospective cohort study framework. This will leverage our RADAR-Base software platform and existing experience working on remote monitoring projects, such as RADAR-CNS [18], and take a similar approach to the major depressive disorder protocol [19]. In addition to this, we have recently developed RADAR-Base capabilities to deliver notifications dependent on real-time processing of participant data streams. This module of RADAR-Base will be evaluated here by deploying an exacerbation detection algorithm (using HR, SpO_2_, and other measures), and participants will be asked in near real time to confirm/reject and score the algorithm’s assertion via a short questionnaire, the Exacerbation Rating Scale (ERS), close to or during the period of exacerbation, in order to provide accurate feedback independent of recall. The ERS scoring will be used to evaluate the algorithm sensitivity/specificity and to evaluate options for personalized exacerbation detection.

Previous studies [12,13] on exacerbations in COPD found that changes in resting heart rate (RHR), pulse oxygen saturation (SpO_2_), and peak airflow are highly correlated with symptoms before, during, and after exacerbation onset, as shown in Figure 1.

Another study [20] looked at the identification and subsequent prediction of exacerbations in COPD. The authors used features derived from pulse oximeters to predict exacerbations using logistic regression. They found that all three vital signs (oxygen saturation, pulse rate, and respiratory rate) are predictors of exacerbations, with oxygen saturation being the most predictive. Another study [21], which looked at the correlation between RHR and acute exacerbations in COPD, found that patients with a higher RHR following exacerbation demonstrated an increased risk of exacerbation.

There is evidence in the literature that pulmonary diseases, like COPD, lung fibrosis, etc, are closely related to the heart [22]. Pulmonary vascular abnormalities are frequently present in patients with respiratory disorders. Similar correlations were found with HR in severe acute respiratory syndrome (SARS), where patients were found to have a high HR and low blood pressure [23].

One interesting and relatively novel approach to understanding the changes in respiratory disorders is through capturing breathing sounds to measure the breathing rate and detect features such as wheezing, coughing, sneezing, and snoring, using audio data. Two exciting works in this field are mLung++ [24] and SonarBeat [25].

The mapping between data types and analytical approaches under consideration is shown in Table 1.

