#### Assess the Potential of Remote Monitoring in COPD, IPF, and COVID-19

The potential of remote monitoring will be evaluated in the context of cardiopulmonary disorders. This will involve developing methods to quantify disease trajectory as compared with standard clinical measures (in IPF, these would be changes in forced vital capacity and death); detecting exacerbations/symptoms, such as changes in wearable data (eg, HR, SpO_2_, and activity), during the reported period of exacerbation (a real-time algorithm will be included to predict exacerbations with patients notified with the ERS to confirm the prediction at or close to the time of the event); detecting exacerbations prior to or after the reported period of exacerbation (eg, a signal that may precede participant awareness of the exacerbation/symptom); detecting subclinical exacerbations in patients with lung fibrosis; tracking self-reported symptoms and outcomes (including precursor presymptomatic signals) and their frequency and order; and reporting longitudinal mental health symptom measures, as reported by the Generalized Anxiety Disorder scale (GAD-7) and Patient Health Questionnaire depression scale (PHQ-8), associated with the three diseases. This will provide the potential to assist with future applications around disease self-management. In the case of the posthospitalization COVID cohort, we will assess whether remote monitoring can be used as a symptom collection tool and as a long-term low-burden monitoring solution. Fatigue will be assessed by Garmin Body Battery values and the Fatigue Severity Scale, while long-term COVID impairments will be measured weekly using the Centers for Disease Control and Prevention (CDC) COVID-19 long-term effects (CCLTE) list, World Health Organization (WHO) symptoms list, and post-COVID functional status (PCFS), a COVID-19-specific widely used questionnaire on health-related impairments (physical functioning scale).

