**Questionnaires - Symptoms, mental health, quality of life (QoL) (aRMT)**					
	Post-COVID-19 functional status (PCFS) scale	Questionnaire/aRMT phone app	Weekly	COVID-19	Establish post COVID-19 functional status [36].
	CDC COVID-19 long-term effects (CCLTE) (aRMT)	Questionnaire/aRMT phone app	Daily	COVID-19	Establish the degree of long-term COVID-19 effects [15].
	WHO COVID-19 symptoms (WCS) list (aRMT)	Questionnaire/aRMT phone app	Daily	COVID-19	Establish the degree of persistent COVID-19 symptoms [37].
	COPD assessment test (CAT)	Questionnaire/aRMT phone app	Cohort: Daily	All	CAT to measure the impact of COPD on a person’s life. It is unidimensional, and assesses cough, sputum, dyspnea, and chest tightness. Eight questions [38,39].
	Idiopathic pulmonary fibrosis patient-reported outcome measure	Questionnaire/aRMT phone app	Weekly	Interstitial lung disease (ILD)	ILD QoL self-report.
	Living with idiopathic pulmonary fibrosis	Questionnaire/aRMT phone app	Daily	ILD	ILD QoL self-report.
	Visual analog scale (VAS) cough	Questionnaire/aRMT phone app	Monthly	ILD	Score symptoms (cough).
	St. George’s Respiratory Questionnaire (SGRQ)	Questionnaire/aRMT phone app	Quarterly	All	Assess the impact of overall health, daily life, and well-being in patients.
	Pittsburgh Sleep Quality Index (PSQI)	Questionnaire/aRMT phone app	Monthly	ILD	Sleep scoring questionnaire.
	Exacerbation rating scale (ERS)	Questionnaire/aRMT phone app	Dynamic/on demand	All	A confirmatory rating scale for detected exacerbations in real time; participants will be sent notifications to complete these.
	Generalized Anxiety Disorder scale (GAD-7) and Patient Health Questionnaire depression scale (PHQ-8) (aRMT)	Questionnaire/aRMT phone app	Fortnightly	All	Establish depressive and anxiety symptoms [40,41].

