We will use the pulse-respiration quotient [44] and pulse-activity quotient as measures of the changes in respiration efficacy and exacerbation.

We will adopt machine learning approaches to perform both cross-sectional and individualized classification for the identification of events, such as exacerbations, using a questionnaire or other active data as labels providing context to passive data streams such as HR, SpO_2_, respiratory rate, and others.

Using multimodal data sets, we will characterize the periods of time around acute events, such as exacerbations, to include the pre-exacerbation period, period during exacerbation, and postexacerbation period.

We will investigate the potential of the data collected to identify putative subclinical exacerbations or other lower level fluctuations in participant symptoms.

If adequate numbers of events are generated in the study, an opportunity to apply anomaly/novelty detection methods will be possible. In this way, we will use these approaches to learn the baseline state for the participants and establish significant deviations from this.

Using the real-time aspect of the data collection, we will use the real-time ERS to acquire real-time responses to evaluate and assess the performance of a model for exacerbation detection and refine an individual-level model for exacerbation detection.

Since we do not have enough prior data, we plan to consider real-time anomaly detection methods and preprocess the data based on prior knowledge. The models will be pretrained on a daily schedule (using previous N days of data; N is yet to be decided but is initially considered 21 days) and will be ready for running inferences in real time (using wearable sensor data as inputs collected in real time) and taking actions based on the results of the inferences (sending an ERS assessment through the aRMT app) to acquire responses at the time of the event to assess the performance of the model.

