**Figure 3 figure3:**
[figure not shown]
Study flow diagram. CAT: COPD assessment test; CCLTE: CDC COVID-19 long-term effects; COPD: chronic obstructive pulmonary disease; EoP: experience of participation; ERS: Exacerbation Rating Scale; FSS: Fatigue Severity Scale; GAD-7: Generalized Anxiety Disorder scale; ILD: interstitial lung disease; IPF: idiopathic pulmonary fibrosis; l-IPF: living with idiopathic pulmonary fibrosis; KBILD: The King's Brief Interstitial Lung Disease; MRC: Medical Research Council; PCFS: post-COVID function status; PHQ-8: Patient Health Questionnaire depression scale; PROM: patient-reported outcome measure; PSQI: Pittsburgh Sleep Quality Index; RADAR: Remote Assessment of Disease and Relapse; SGRQ: St. George's Respiratory Questionnaire; TAMF: Technology Acceptance Model Fast Form; VAS: visual analog scale; WCS: World Health Organization COVID-19 symptoms.

The wearable device provided to participants connects to the wearable vendor’s application, and the data are uploaded to the vendor’s server, which is then synchronized to the RADAR-Base platform. On getting all the data, the RADAR-Base platform runs real-time data processing, and based on a threshold for exacerbation, it sends a notification and assessment for confirmation of the exacerbation in the form of the ERS. On exit or completion of the study, the participants will be asked about their experiences with the technology and the study.

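### The ERS asks participants to confirm or reject the algorithm's own alert, so the rating used to judge the detector is given with knowledge of its result, and the confirmed share is open to bias of unknown net direction

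*Protocol article*

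**What the plan says.** Four places in the protocol article describe the same sequence.

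- Study Flow Chart (text with Figure 3): the platform processes the data and "based on a threshold for exacerbation, it sends a notification and assessment for confirmation of the exacerbation in the form of the ERS".
- Theoretical Framework: "participants will be asked in near real time to confirm/reject and score the algorithm’s assertion via a short questionnaire".
- Outcomes, on the potential of remote monitoring: "a real-time algorithm will be included to predict exacerbations with patients notified with the ERS to confirm the prediction".
- Table 2: the ERS is "A confirmatory rating scale for detected exacerbations in real time; participants will be sent notifications to complete these".

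Two places say what the answers are for. Theoretical Framework: "The ERS scoring will be used to evaluate the algorithm sensitivity/specificity and to evaluate options for personalized exacerbation detection". Data Analysis: the real-time responses are to "evaluate and assess the performance of a model for exacerbation detection and refine an individual-level model for exacerbation detection".

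Theoretical Framework justifies the prompt timing on the ground that the feedback will not depend on recall. The article does not describe hiding the alert from the participant, wording the prompt neutrally, or sending the ERS when there has been no alert.

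**The concern.** In a study of detection accuracy, the reference rating should be made without knowledge of the index result. Here the participant is the rater, learns that the algorithm has flagged an exacerbation, and is asked whether it is right. Rating close to the event deals with recall error only.

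Suggestion is plausible in these cohorts. The COPD background section describes daily symptoms outside exacerbations, and Table 3 admits post-COVID participants because their symptoms interfere with daily activity. A participant told of a detection will often have some symptom to attribute to it.

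Two things are at stake. The apparent performance of the alerts may not reflect their true performance. In addition, the same answers train the personalised models, so wrong labels can carry into later detection. An analysis plan could not undo this once the answers have been collected.

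**Working it through.** The protocol states no confirmation rate, alert rate, predictive value, sensitivity or specificity, so there is no figure to reproduce. The numbers below are assumptions, used to show how the confirmed share behaves.

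**Inputs (all assumed)**

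- p: the true share of alerts that are exacerbations
- c1: the proportion of true alerts that participants confirm
- c0: the proportion of false alerts that participants confirm

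**Formula**

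Observed share confirmed = p × c1 + (1 − p) × c0.

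**Results for p = 0.30**

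| c0 | c1 = 1 | c1 = 0.70 |
|---|---|---|
| 0.10 | 0.30 + 0.07 = 0.37 | 0.21 + 0.07 = 0.28 |
| 0.20 | 0.30 + 0.14 = 0.44 | 0.21 + 0.14 = 0.35 |
| 0.30 | 0.30 + 0.21 = 0.51 | 0.21 + 0.21 = 0.42 |

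If every true alert is confirmed, any agreement with false alerts raises the share above 0.30. If 30% of true alerts are rejected, the share can fall below the truth (0.28).

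The second column matters because of the protocol's own aims. The Outcomes section seeks "a signal that may precede participant awareness of the exacerbation/symptom", and both Outcomes and Data Analysis seek subclinical exacerbations. A participant who feels nothing may reject such an alert although it is true.

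**Where the sign changes**

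The observed share exceeds p only if c0 > p × (1 − c1) / (1 − p). With c1 = 0.70:

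- p = 0.20: 0.06 / 0.80 = 0.075
- p = 0.30: 0.09 / 0.70 = 0.13
- p = 0.40: 0.12 / 0.60 = 0.20
- p = 0.60: 0.18 / 0.40 = 0.45
- p = 0.80: 0.24 / 0.20 = 1.2, which no proportion can reach, so the share is always too low

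**Two separate effects**

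Telling participants of a detection should raise c1 and c0 relative to a neutral form, so disclosure by itself probably pushes the share up. Rejection of alerts that precede awareness lowers c1 and pushes it down. The documents give nothing from which to size either effect, and there is no reason to expect them to cancel.

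**The case against.** A reader might infer that the confirmed share is inflated as a matter of fact. The documents do not support this. That reading needs every true alert to be confirmed, while the protocol deliberately looks for events the participant may not yet feel.

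A reader might also infer that the question leads towards yes. Neither the ERS items nor the notification text is reproduced, and the description offers both confirming and rejecting, plus a score. It supports a finding that the rating is not blind, but not that the wording is leading.

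Other labels exist. Table 1 lists questionnaires, tasks, an event diary and spirometry. Table 2 schedules daily spirometry and a daily COPD Assessment Test (CAT). The COPD cohort section uses patient report to a clinician as the comparator for earlier detection. None of these is described as triggered by an alert. This stands as mitigation and supplies part of the remedy, but Theoretical Framework names the ERS for sensitivity and specificity, and Data Analysis names it for assessing and refining the real-time model.

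The point also overlaps with the fact that the ERS is described only after alerts, which leaves missed events and true negatives without an ERS rating. The two share a remedy and should not be counted twice at full weight. They are still different faults: one concerns ratings never obtained, the other the validity of those that are.

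Finally, this is a feasibility pilot of 20 participants per cohort, event identification is exploratory, and participants are told that their data will not prompt clinical action. That limits the harm. It does not remove the fault, since detection of exacerbations is part of the evaluation under the primary objective.

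**Conclusion.** The point holds in a limited form. As described, the ERS rating is given with knowledge of the index result, and that rating is the named reference for the detector and an input to its refinement. The confirmed share is open to suggestion bias. Disclosure probably acts upward, but the net direction and size against the true share cannot be fixed from the documents. Under the assumptions above, a true share of 0.30 could appear as anything from 0.28 to 0.51.

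The conclusion rests on the article's description of the task. If the deployed form is neutrally worded and does not disclose the detection, the concern is smaller, although receipt of a form sent only after alerts could still reveal one. The change is worth making because it is cheap. The fault does not undermine the study's assessment of feasibility and acceptability.

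**What to change.** 1. Present the ERS as a neutral rating of current symptoms against the participant's usual state. The notification and form should not mention a detection or prediction, and there should be no confirm/reject item.
2. Send the same form at some non-alert times, so that receiving it does not reveal an alert, and say in the information sheet that timing is partly random. Rewording alone would not blind the rater.
3. Derive exacerbation status from the scores by a rule fixed in advance and applied without sight of the alert.
4. Also assess alerts against labels already collected that are not described as alert-triggered: the scheduled daily CAT where collected, the event diary, and patient report to a clinician. This step also helps with true alerts that precede awareness, which a neutral form alone would not resolve.

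The cost is more than a change of wording. It adds a few prompts where Table 4 already rates participant fatigue a medium risk, needs a scoring rule that the article does not give, and changes the training session and information sheet. It probably also needs an ethics amendment, since Progress to Date reports approval obtained and recruitment under way. The same section says that algorithm development is still in progress, and Table 4 allows active data collection to be adapted during the study, so the change remains practicable.
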